**Method:**

In this pilot study comparing the effectiveness of an adapted 7-week iCBT without main carer access against the iCBT with main carer access and treatment-as-usual control, 108 breast cancer survivors will be recruited and then randomised to either (1) treatment (*n* = 72) or (2) treatment-as-usual control group (*n* = 36) with a 2:1 ratio. The participants in the treatment group will be assigned to either iCBT alone or iCBT with the main carer also having access to the same content based on their preference. The primary outcome measure is the Hospital Anxiety and Depression Scale, and alongside secondary measures such as Cancer-Related Quality of Life, Breast Cancer Worry Scale, Brief COPE, and Medical Outcomes Study Social Support Survey will be completed by the survivors at baseline, post-treatment, and 2-month follow-up. Survivors who have carers will also complete Survivor-Carer Cancer Communication and Relationship Quality measures to provide insights into the effects of carer access. To assess the acceptability and satisfaction with the programme, survivors and their main carers will fill out the Helpful Aspects of Therapy Form (HAT) and Satisfaction with Online Treatment (SAT). Programme effectiveness and the effects of carer access on primary and secondary outcome measures will be evaluated on intention-to-treat and per-protocol basis using Linear-Mixed-Models.

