### Aims of the study

1.4

The present pilot study has six aims:a)To evaluate the effectiveness of an adapted iCBT on the treatment of breast cancer survivors' depression and anxiety symptoms in response to the treatmentb)To determine any changes in breast cancer survivors' quality of life, coping, fear of cancer recurrence in response to the treatmentc)To evaluate any changes in breast cancer survivors' perceived social support, cancer communication, and relationship quality in response to the carer access to survivors' treatment contentd)To evaluate any changes in carers' cancer communication and relationship quality in response to their access to survivors' treatment contente)To compare the effects of an adapted iCBT with and without main carer access on breast cancer survivors' depression and anxiety symptomsf)To evaluate the helpful aspects of the iCBT intervention and satisfaction with the programme among breast cancer survivors and their main carers

Therefore, breast cancer survivors will be randomly assigned to either iCBT intervention or treatment-as-usual control. The survivors assigned to the iCBT intervention group and who have a carer will be asked their preference to give their carers access to the intervention programme content. The iCBT group will be allocated to either iCBT alone or iCBT with carer access based on their preference. Therefore, there will be 3 groups in total.

Group 1: iCBT alone

Group 2: iCBT with carer access

Group 3: Treatment-as-usual control

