### Hypotheses and research questions

1.5

Hypothesis about the primary outcomes:**H1**Survivors in both treatment groups (Group 1 and Group 2) are expected to show a greater reduction in depression and anxiety symptoms than survivors in the TAU (Group 3) at post-treatment and 2-month follow-up.

Hypotheses about the secondary outcomes:**H2**Survivors in both treatment groups (Group 1 and Group 2) are expected to have greater improvements in cancer-related quality of life, coping, and fear of recurrence compared to survivors in the TAU (Group 3) at post-treatment and 2-month follow-up.**H3**Survivors in both treatment groups (Group 1 and Group 2) are expected to use more active coping strategies than survivors in the TAU (Group 3) at post-treatment and 2-month follow-up.**H4**A reduction in depression and anxiety symptoms of survivors in both treatment groups (Group 1 and Group 2) is expected to be mediated by the change in coping strategies after controlling for depression and anxiety levels at baseline.**H5**An improvement in cancer-related quality of life in both treatment groups (Group 1 and Group 2) will be mediated by the change in coping strategies after controlling for cancer-related quality of life at baseline.

The effects of carer access will be explored using the following research questions:

**RQ1.** Is there a difference in depression and anxiety scores between iCBT alone (Group 1) and iCBT with the carer access (Group 2) at post-treatment after controlling for baseline depression and anxiety scores?

**RQ2.** Is there a difference in perceived social support between iCBT alone (Group 1) and iCBT with the carer access (Group 2) at post-treatment after controlling for baseline perceived social support?

**RQ3.** Is there a difference in survivor-carer relationship outcomes (cancer-related communication quality and relationship quality) of survivors in iCBT with carer access between baseline and post-treatment?

**RQ4.** Is there a difference in survivor-carer relationship outcomes (cancer-related communication quality and survivor-carer relationship quality) of carers between baseline and post-treatment?

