### Randomisation

2.5

Eligible participants will be randomly assigned to either iCBT intervention (n = 72) or treatment-as-usual control (*n* = 36) with a 2:1 ratio. Those who are assigned to iCBT group and have carers will be asked whether they will participate with or without their main carer. Participants will be assigned to iCBT alone or iCBT with carer access based on their preference and informed immediately about their group assignment. Survivors in the iCBT alone group (Group 1) will be using the iCBT programme by themselves, and survivors in the iCBT with the main carer access group (Group 2) will be using the same programme, but their main carers will also have access to the programme content using a separate username and password. Participants in the treatment-as-usual control group (Group 3) will continue their usual care and will not receive the iCBT programme during this study. They will fill out the same measures as the other two groups at pre-treatment, post-treatment, and 2-month follow-up.

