#### Analyses exploring the effects of carer access

2.10.3

LMM will be used to explore whether there are differences in depression and anxiety scores and perceived social support of survivors who used the iCBT programme alone and survivors who used the iCBT programme with carers having access at post-treatment. To account for the potential confounds, baseline levels of perceived social support will be controlled when comparing the iCBT alone and iCBT with the carer access groups. Those who have someone to care for them may perceive higher social support prior to the iCBT intervention and the initial levels may influence responses to the iCBT programme. LMM will also be used to evaluate whether there are differences in survivors' and their carers' communication quality and relationship quality scores at post-treatment after controlling for baseline scores.

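### RQ3 asks about an effect of carer access but tests only the before-after change in Group 2, and section 2.10.3 describes a different analysis with no named comparator

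*Protocol article*

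**What the plan says.** All references are to the protocol article.

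- **Section 1.4, aim (c)** concerns changes in survivors' perceived social support, "cancer communication, and relationship quality in response to the carer access". Aim (d) makes the same attribution for carers' own communication and relationship scores.
- **Section 1.5** introduces RQ1 to RQ4 with "The effects of carer access will be explored using the following research questions". RQ2 is a comparison "between iCBT alone (Group 1) and iCBT with the carer access (Group 2) at post-treatment after controlling for baseline perceived social support", and RQ1 has the same form. RQ3 asks about a difference "of survivors in iCBT with carer access between baseline and post-treatment", and RQ4 about a difference "of carers between baseline and post-treatment". Neither names a second group.
- **Section 2.10.3** says mixed models will evaluate differences in survivors' and carers' "communication quality and relationship quality scores at post-treatment after controlling for baseline scores". It does not say which groups are compared on these outcomes.
- **Who is measured.** The Abstract (Method) states: "Survivors who have carers will also complete Survivor-Carer Cancer Communication and Relationship Quality measures". Section 2.6 places both measures in the baseline set completed before randomisation and has all survivors reassessed. Section 2.5 says of the treatment-as-usual (TAU) group: "They will fill out the same measures as the other two groups at pre-treatment, post-treatment, and 2-month follow-up". Carers are contacted only when the survivor has chosen carer access (section 2.6).
- **Status.** Sections 2.1 and 3 call the carer-access analyses exploratory, possibly underpowered and to be read with caution.

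**The concern.** Survivors in Group 2 get two things at once: the guided programme, and a carer who can see it. Section 1.3 says content on emotional expression and effective listening was added during the adaptation, and Module 2 in Table 1 encourages users to express emotions. Section 2.9.3.5 says the communication measure was chosen because its items cover what the adaptation addressed. The authors therefore have reason to expect the programme alone to move this outcome. A before-after change in Group 2 cannot tell that effect, or the passage of seven weeks, from an effect of carer access.

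The risk is that an improvement in Group 2 is reported as a response to carer access when it would have occurred without it. The contrast is also unsettled: an analyst following section 1.5 and one following section 2.10.3 could run different analyses and report different answers to the same question.

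**Working it through.** The plan gives no figure for this contrast, so there is none to reproduce. The check sets the sections side by side and then illustrates the size of the problem.

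**Step 1: the contrasts**

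| Item | Outcome | Contrast stated | Comparator |
|---|---|---|---|
| RQ1 | depression and anxiety | Group 1 vs Group 2, post-treatment, baseline-adjusted | Group 1 |
| RQ2 | perceived social support | Group 1 vs Group 2, post-treatment, baseline-adjusted | Group 1 |
| RQ3 | survivors' communication and relationship quality | Group 2, baseline vs post-treatment | none |
| RQ4 | carers' communication and relationship quality | carers, baseline vs post-treatment | none |
| Section 2.10.3 | both sets of relationship outcomes | post-treatment, baseline-adjusted | not named |

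RQ3 is the only survivor question without a comparator. Survivors with a carer exist outside Group 2, since those randomised to iCBT may have a carer and decline access (sections 1.4 and 2.5), and they and TAU survivors with a carer complete the same measures.

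**Step 2: how often shared change would look like an access effect**

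Inputs:
- n = 27, the planned per-group number after attrition (section 2.4). Group 2's real size depends on preference.
- Two-sided alpha 0.05.
- Assumptions not in the documents: true access effect zero; change common to all groups 0.3 SD; pre-post correlation r from 0.3 to 0.7; equal SDs at both times.

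The SD of the change, in units of the outcome SD, is √(2(1 − r)). The noncentrality of the paired t test is 0.3 × √27 / √(2(1 − r)), with 26 degrees of freedom and critical value 2.056.

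| r | SD of change | Noncentrality | P(p < 0.05) |
|---|---|---|---|
| 0.3 | 1.183 | 1.317 | 25% |
| 0.5 | 1.000 | 1.559 | 32% |
| 0.6 | 0.894 | 1.743 | 39% |
| 0.7 | 0.775 | 2.012 | 49% |

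At r = 0.6 the rate is 30% with n = 20 and 50% with n = 36.

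**Step 3: what a controlled contrast could detect**

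For a baseline-adjusted comparison of two groups of 27, the standard error is √((1 − r²)(1/27 + 1/27)) in SD units. With 51 degrees of freedom, 80% power requires a difference of 2.856 standard errors.

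| r | Standard error | Detectable difference |
|---|---|---|
| 0.3 | 0.260 | 0.74 SD |
| 0.5 | 0.236 | 0.67 SD |
| 0.7 | 0.194 | 0.56 SD |

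If only 15 Group 1 survivors had a carer (an assumption), the same formula gives 0.88, 0.80 and 0.66 SD. This contrast removes the change common to both iCBT groups, but it is imprecise.

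**The case against.** The strongest reply is that section 2.10.3 already contains the right analysis. Its sentence on communication and relationship quality comes in a paragraph about comparing iCBT alone with iCBT plus carer access, and it uses the post-treatment, baseline-adjusted form of RQ1 and RQ2. It can be read as a between-group comparison. That stands, so the documents do not support a flat statement that the comparator data will go unused. But no group is named for these outcomes, RQ3 states a one-group change, and the two must be reconciled.

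A second reply is that these analyses are declared exploratory and will be interpreted with caution. This lowers the consequence. The stated reasons are preference-based allocation and low power, however, and neither tells a reader that RQ3 has no comparator.

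A third reply is that the controlled contrast has its own bias. Group 1 survivors with a carer chose not to share access, and that choice may depend on the relationship being measured. TAU survivors with a carer mix would-be sharers and non-sharers. This stands in full and has to be stated with any result. RQ1 and RQ2 already accept the same limitation.

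Three stronger readings are tempting and should not be drawn:
- *Aim (c) cannot be answered at all.* RQ2 addresses its social-support part with a between-group contrast.
- *Adjusting for baseline in a single group leaves nothing to test.* If change is regressed on mean-centred baseline, the intercept is the mean change and can be tested.
- *Regression to the mean would produce a false improvement.* Section 2.2 sets no entry threshold on these scores, so nothing selects survivors with poor values.

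**Conclusion.** The point holds for RQ3. As written, it cannot separate carer access from the iCBT programme or from time, and section 2.10.3 does not clearly replace it. The communication and relationship parts of aim (c) are affected.

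Under the stated assumptions (n = 27, no access effect, shared change of 0.3 SD), the before-after test would be significant in about 25% to 49% of trials for correlations of 0.3 to 0.7. The size of the shared change and the correlation are not in the documents, so these figures show the mechanism and do not predict the trial's result. The conclusion itself rests on the wording of the sections and does not depend on them.

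RQ4 is also uncontrolled, but no carers outside Group 2 are surveyed, so only its interpretation can be changed. Because the analyses are exploratory, this should be corrected but does not threaten the primary comparison.

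**What to change.** 1. **RQ3 and section 2.10.3.** State one contrast in both places: a baseline-adjusted linear mixed model comparing Group 2 with Group 1 survivors who have a carer, at post-treatment, in the form of RQ1 and RQ2. Give TAU survivors who have a carer as a supporting reference.
2. **Caveat.** Say that these contrasts are preference-based, non-randomised and exploratory. Say also that they are imprecise: about 0.56 to 0.74 SD detectable at 27 versus 27 for correlations of 0.3 to 0.7, and larger if few Group 1 survivors have a carer. Report estimates with confidence intervals.
3. **RQ4 and aim (d).** Report carers' change from baseline with a confidence interval as descriptive, and remove from aim (d) the wording that attributes the change to their access.

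The cost is rewording of sections 1.4, 1.5 and 2.10.3. The survivor data are already planned, and no new measures or participants are needed.

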## Methods and design

2

### Study design

2.1

This study is comparing 7-module iCBT with guidance against iCBT with main carer access and treatment-as-usual control among women living with breast cancer who completed their treatment. Both immediate treatment groups will be followed up until 2 months post-treatment. This is a pragmatic pilot trial as survivors' allocation to the iCBT alone or iCBT with the carer access group will be based on survivors' preference. Therefore, the effects of being in the iCBT with the carer access arm are examined in an exploratory manner using research questions rather than confirmatory hypotheses testing. Fig. 1 shows the outline of the trial design in detail.

**Fig. 1 f0005:**
[figure not shown]
Participant flow chart.

### Study setting and participants

2.2

Participants will be recruited online from across Ireland and will be screened for eligibility. Inclusion criteria for survivors are (1) being female, (2) having completed the active breast cancer treatments such as chemotherapy, radiotherapy, and surgery (participants could be on hormone therapy) and being cancer-free, (3) being at least mildly confident with using the internet, and (4) being at least mildly confident in reading and writing in English.

Inclusion criteria for main carers are (1) currently caring or have cared for a woman living with breast cancer (such as a partner, spouse, friend, or relative), (2) being at least mildly confident with using the internet, and (3) being at least mildly confident in reading and writing in English.

Exclusion criteria for breast cancer survivors and carers are (1) current suicidal ideation or intent, (2) current alcohol or drug misuse, (3) enduring mental health disorders such as schizophrenia, psychosis, and bipolar disorder, and (4) currently being in psychological treatment for depression or anxiety. As it is a pilot study, no limit has been set for the time since the treatment completion or cancer stage as an exclusion criterion for survivors.

### Recruitment

2.3

Participants will be recruited through online cancer support groups, cancer research email listings, flyers, posters, and internet social media advertising (Facebook and Twitter). A Qualtrics link will be provided on the advertisement and via email. All survivors who show an interest in this trial will be able to read the Information Leaflet and sign the informed consent through the provided Qualtrics survey link.

### Sample size

2.4

The G-Power software programme was used to carry out power analysis and determine the sample size needed for three-group, pre-test, post-test, and follow-up design. The data from a randomised controlled trial of an iCBT programme for depression and anxiety among cancer survivors revealed a large within-between interaction effect size for the HADS-Total after comparing the pre-treatment and post-treatment scores of the iCBT and the TAU (Murphy et al., 2019). To calculate the sample size, we powered for the changes in the primary outcome (depression and anxiety symptoms, measured by the HADS-Total) when comparing the treatment groups (iCBT alone and iCBT with the carer access) with the TAU. Assuming a medium effect size (*f* = 0.30) for the pre, post, follow-up comparisons between iCBT alone, iCBT with carer access, and TAU with a power of 0.80 and significance level of α = 0.05, the sample size is calculated to be 27 breast cancer survivors in each group and 81 in total (54 in the iCBT group and 27 in the TAU group using 2:1 ratio). Considering the 25% attrition (Richards et al., 2018), 108 breast cancer survivors in total (*n* = 72 for iCBT and = 36 for TAU) will be recruited.

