Women with breast cancer often deal with this stressful experience by turning to their partners or spouses (Manne et al., 2016; Salakari et al., 2017), or their close relatives, and friends for emotional support (Ockerby et al., 2013); usually one of these people will assume a caregiver role (Tiete et al., 2020). Social support from significant others is one of the most important determinants of patients' positive psychological adjustment and lower psychological distress (Helgeson et al., 2004; Hughes et al., 2014; Ng et al., 2015; Thompson et al., 2017). Open and mutual communication about cancer-related issues and concerns between patients and carers has been associated with less distress and greater relationship satisfaction for both patients and their partners (Manne et al., 2006). A recent randomised controlled study suggested that encouraging cancer patients and carers to express their personal cancer-related concerns helps improve their coping ability with the illness (Tiete et al., 2020). Active participation of the carer in the intervention through a couple-based intervention might help improve the quality of life, psychological distress, and relationship functioning of couples coping with breast cancer as demonstrated by a systematic review (Brandão et al., 2014). However, couple-based interventions for cancer have lower uptake rates than individual-based interventions, especially when both the patient and the carer are required to participate in the intervention simultaneously (Hopkinson et al., 2012; Regan et al., 2013).

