Secondly, no study to date has examined the effectiveness of including informal carers in the survivors' intervention programme targeting their depression and anxiety symptoms. This pilot trial is novel as it further aims to explore whether giving main carers (i.e., partners, family members, friends) access to survivors' iCBT treatment makes a difference on survivors' anxiety and depression symptoms, social support perceptions, and cancer-related communication quality, and relationship quality with their carers as well as carers' cancer-related communication quality, and relationship quality with survivors. This study will provide novel insight regarding the feasibility of carer access based on the number of survivors who prefers to give their carers access to the iCBT programme. The trial is sufficiently powered for testing the primary and secondary hypotheses, and analyses regarding the effects of the iCBT with the carer access are more exploratory. As the iCBT alone and iCBT with the carer access group assignment is based on survivors' preference due to its exploratory nature, the study may be underpowered for detecting those effects in the exploratory analyses. Therefore, the results of the exploratory analyses will be interpreted with caution.

Another notable strength of this study is that it uses a mixed-methods approach by combining quantitative methods to measure the programme effectiveness with qualitative measures through HAT and SAT to assess the user experiences and satisfaction, which will provide rich information and help us to better understand the nature of the existing relationship between outcomes. If the programme is found feasible and a clinically significant difference is found in depression and anxiety symptoms of survivors, the iCBT programme may be used as an alternative within stepped care of breast cancer patients and survivors, where guided low-intensity interventions are an attractive option (Richards et al., 2018).

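### 27 women per group is not secured for the two iCBT groups, which form by preference, so the power claim is supported only for pooled iCBT against TAU

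*Protocol article*

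**What the plan says.** - **Sizing (2.4).** The calculation was done to "determine the sample size needed for three-group, pre-test, post-test, and follow-up design". It is described as powering HADS-Total "when comparing the treatment groups (iCBT alone and iCBT with the carer access) with the TAU", with f = 0.30 "for the pre, post, follow-up comparisons between iCBT alone, iCBT with carer access, and TAU", power 0.80 and alpha 0.05. The result is that "the sample size is calculated to be 27 breast cancer survivors in each group and 81 in total". The same sentence also gives it as 54 iCBT and 27 TAU. With 25% attrition, 108 are recruited (72 and 36).
- **Allocation (2.5).** Only iCBT v TAU is randomised, 2:1. Then "Participants will be assigned to iCBT alone or iCBT with carer access based on their preference". Only iCBT women who have a carer are asked. No quota, cap or expected uptake is given.
- **Primary hypothesis (1.5).** H1 reads: "Survivors in both treatment groups (Group 1 and Group 2) are expected to show a greater reduction in depression and anxiety symptoms" than TAU. H2 and H3 name the same two groups.
- **Analysis (2.10.2).** The linear mixed model has three groups. Intention-to-treat is defined by the arm to which a woman was randomised, which can only be iCBT or TAU.
- **Power statement (3 Discussion).** "The trial is sufficiently powered for testing the primary and secondary hypotheses". The possible loss of power from preference allocation is acknowledged only for the exploratory carer-access analyses.

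**The concern.** The sizing gives a number for each of three groups, but the design controls only two. How many of the 54 evaluable iCBT women fall in Group 1 or Group 2 is an outcome of the trial: the Discussion itself treats the number choosing carer access as something the study will learn. Either group could fall short, Group 2 if uptake is low and Group 1 if it is high.

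Whether this matters for H1 depends on a choice the protocol leaves open. Sections 1.5 and 2.10.2 name the groups separately, which suggests two contrasts with TAU. The 54 v 27 statement and intention-to-treat by randomised arm permit a single pooled contrast. Under the first reading, the Discussion's power claim covers contrasts whose group sizes nobody has fixed. A Group 2 v TAU result that missed significance because few women chose carer access could then be taken as failure of part of a confirmatory hypothesis that the protocol describes as adequately powered.

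**Working it through.** **1. The plan's own figures.**
- Attrition: 81/0.75 = 108, 54/0.75 = 72, 27/0.75 = 36. These reproduce.
- The 81 cannot be confirmed, because neither the test family nor the correlation ρ between repeated measures is stated. With f = 0.30, three groups, three times, alpha 0.05 and power 0.80, a between-factors test gives 75 at ρ = 0.50, 81 at ρ = 0.55 to 0.59, and 84 at ρ = 0.60. The group-by-time interaction at ρ = 0.50 gives 27 in total, not per group.

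**2. An effect that takes the 80% claim at its word.** Assume that both iCBT groups differ from TAU in change from baseline by d (in SD of the score), equally at post-treatment and follow-up. The noncentrality of the 4-df group-by-time test is

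λ = (54 × 27/81) × (2/3) × d²/(1 − ρ) = 12d²/(1 − ρ).

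Solving for 80% power at 27/27/27 (4 and 156 df) gives d = 0.716 at ρ = 0.5 and 0.555 at ρ = 0.7. Only 54 and 27 enter λ, so with equal effects this omnibus test has the same power for any split of the iCBT arm.

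**3. Contrasts with TAU at post-treatment.** The SD of change is √(2(1 − ρ)), which is 1 at ρ = 0.5. The noncentrality for a group of size n is d/√(1/n + 1/27), tested two-sided at 0.05:
- n = 27: 0.716/0.272 = 2.63
- n = 18: 0.716/0.304 = 2.35
- n = 14: 0.716/0.329 = 2.17
- n = 10: 0.716/0.370 = 1.93
- pooled n = 54: 0.716/0.236 = 3.04

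Powers come from 200,000 simulated trials per split, with the TAU group shared between contrasts. The splits are assumptions.

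| Group 1 / Group 2 / TAU | Group 2 v TAU | Both groups beat TAU | Pooled iCBT v TAU |
|---|---|---|---|
| 27/27/27 | 74% | 61% | 85% |
| 36/18/27 | 64% | 57% | 85% |
| 40/14/27 | 57–58% | 52% | 85% |
| 44/10/27 | 48% | 44% | 85% |

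The powers at ρ = 0.7 are the same. By symmetry, a 14/40 split gives the same joint figure, with Group 1 as the small group.

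**4. A second route.** Use the between-factors test at ρ = 0.57, where 81 does reproduce, and d = 0.30/√(2/9) = 0.636. Group 2 v TAU has 78%, 69%, 62% and 52% at 27, 18, 14 and 10 women. Pooled iCBT v TAU has 88% and the omnibus test 81% at every split. The pattern is the same.

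**5. f = 0.30 read literally as the interaction effect.** Equating 81 × 3 × f² with 12d² gives d = f × √(243/12) = 4.5 × 0.30 = 1.35 SD. At 40/14/27 the chance that both groups beat TAU at post-treatment is then about 98%, and at 44/10/27 about 95%.

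**The case against.** **H1 can be read as pooled.** Section 2.4 gives 54 v 27, and intention-to-treat follows the randomised arm. On that reading the split has no effect on H1. This stands. It makes the defect an unstated choice of contrast, together with a power claim that does not say which contrast it covers.

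**Carer access is already declared exploratory.** Section 2.1 says so because of preference allocation, and the Discussion promises caution. This softens the risk of misreading. But those statements chiefly introduce the Group 1 v Group 2 and within-group research questions, while H1 to H3 still name Group 2 among the confirmatory hypotheses.

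**Low uptake is not shown.** A reader might infer that Group 2 will fall well below 27, since the Background says that "couple-based interventions for cancer have lower uptake rates than individual-based interventions". The documents do not support this. The same sentence stresses simultaneous participation, and the Background goes on to argue that access without simultaneous log-in may appeal more to carers. No uptake figure is given.

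**The shortfall needs an effect that the protocol does not state.** This is correct: 0.716 SD is back-solved, and step 5 shows ample power if f = 0.30 is the interaction effect. But on that reading the required total at ρ = 0.50 is 27, so it does not explain 81.

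**Preference is not the main driver.** This is also fair. Joint power is already about 61% at 27/27/27, because an omnibus calculation does not secure 80% for two separate contrasts. Uneven uptake lowers it further.

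**Conclusion.** The point holds in limited form. Twenty-seven women in each iCBT group is not secured, and the protocol does not say whether H1 is one pooled contrast or two separate ones. If each group must beat TAU, the Discussion's power claim is not secured: joint power at post-treatment is about 61% at 27/27 and about 52% at an assumed 40/14 split. Pooled iCBT v TAU keeps about 85% for any split.

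These figures rest on equal effects in both iCBT groups and at both later times, two-sided alpha 0.05, 81 evaluable women, and an effect chosen to give the omnibus interaction test 80% power. At a literal interaction effect of f = 0.30 there is no practical shortfall at the splits examined.

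It would go too far to conclude that the plan cannot deliver 27 and 27, or that the trial is underpowered for iCBT against TAU. The first is unknown, and the second is contradicted by the pooled figure at the effects considered. The correction is worth making because it concerns a figure and a claim on which the trial's confirmatory reading relies.

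**What to change.** - **1.5 and 2.10.2:** make the primary H1 contrast pooled iCBT v TAU as randomised, estimated within the existing three-group mixed model.
- **2.4:** state the sizing as 54 v 27 evaluable, and drop 27 as a target for Groups 1 and 2.
- **3 Discussion:** limit the statement of adequate power to that contrast on HADS-Total. Extend the existing caveat about low power to Group 1 v TAU and Group 2 v TAU, and report both with confidence intervals.

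This costs wording only, with no extra participants and no change to randomisation or data collection. The price is that the per-group parts of H1 to H3 become supportive rather than confirmatory.
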